|                 |                                                                                                                                                                                                                                                                                                                                                                                                                                                                                                 |
|-----------------|-------------------------------------------------------------------------------------------------------------------------------------------------------------------------------------------------------------------------------------------------------------------------------------------------------------------------------------------------------------------------------------------------------------------------------------------------------------------------------------------------|
|                 | 
therapy group (Tashiro et al., Transplantation, 2011).
 
Based on these results, the expected incidence of bacteremia in NK therapy at 1 month after living donor liver transplantation was set at 10%, and the number of cases required to examine the threshold of 30% incidence in non-NK therapy at 5% significance level (both sides) and 80% power was calculated to be 34. Considering the dropout cases at the time of enrollment, we set the target number of cases at 37.
 |
| Research period | 
Research period: From the date of research notification to December 31, 2024 (9 years)
 
Period of case registration: From the date of research notification to December 31, 2021 (6 years)
                                                                                                                                                                                                                                                                                         |

schema

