## 11 Criteria and procedures for discontinuation of clinical research for each subject

### 11.1 Criteria for discontinuation of clinical research for each subject

The principal investigator or sub-investigator shall discontinue or suspend clinical research on the subject in the following cases

1. If a positive test is found in the infectious disease test of culture test material.
2. In addition to 1) above, if protocol treatment is no longer possible
3. When a subject requests withdrawal of consent for participation in clinical research.
4. When the occurrence of an adverse event is recognized and the principal investigator judges that it is difficult to continue the clinical research on the subject concerned.
5. If it is discovered after enrollment but before the start of protocol treatment that the subject did not meet the eligibility criteria
6. In other cases, when the principal investigator or sub-investigator deems it appropriate to discontinue the clinical research.

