### 15.2 Definition of the population for analysis

#### 15.2.1 Efficacy analysis population

Subjects who are enrolled in this clinical study and underwent living partial liver transplantation and NK cells were administered on postoperative day 3 will be the target population for efficacy analysis (the largest analysis set Full Analysis Set: FAS).

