### 15.3 Handling of missing values

Withdrawals due to discontinuation or deviations during the course of the study will be reported to the

- ✓ The data observed immediately before the subject's discontinuation or dropout will be analyzed as the last observation data (Last Observation Carried Forward: LOCF).
- ✓ Analysis based on observed values without supplementing missing data (Observed Case: OC)
- ✓ Discontinuation and dropout cases will be analyzed as treatment failure cases (bacteremia cases/ Failure).

The robustness of the results of the analysis by the method of the primary endpoint will be confirmed. The primary endpoint will be analyzed as a failure (failure).

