## 15.5 Efficacy analysis

### 15.5.1 Primary endpoints

Incidence of bacteremia within 1 month after living donor liver transplantation  
[Main analysis]

The incidence of bacteremia within 1 month after living donor liver transplantation and its 95% confidence interval will be calculated for FAS. In addition, the following statistical hypothesis test will be performed at a significance level of 5% (two-tailed) by chi-square test using the 30% incidence of bacteremia with non-NK therapy observed in previous studies as a threshold.

The null hypothesis: "The incidence of bacteremia  $p$  in NK therapy is equal to a threshold of 30% ( $p = 0.3$ )."

Counter-hypothesis: "The incidence of bacteremia  $p$  in NK therapy is less than the threshold of 30% ( $p < 0.3$ )"

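### The stated 80% power ignores the rule that dosed dropouts count as bacteremia, and by exact calculation it is 75% once the 34-to-37 allowance is used

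*Protocol*

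**What the plan says.** The planning assumptions are in the Protocol Overview and again in section 7.2. The rate under treatment: "the expected incidence of bacteremia in NK therapy at 1 month after living donor liver transplantation was set at 10" (per cent). The comparator: "the number of cases required to examine the threshold of 30% incidence in non-NK therapy". The result: "5% significance level (both sides) and 80% power was calculated to be 34". The allowance follows: "Considering the dropout cases at the time of enrollment, we set the target number of cases at 37". No dropout rate is given.

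Section 15.5.1 runs the main analysis on the FAS, with a test "performed at a significance level of 5% (two-tailed) by chi-square test using the 30% incidence of bacteremia with non-NK therapy". Section 15.2.1 restricts the FAS to enrolled, transplanted recipients who were infused: "NK cells were administered on postoperative day 3 will be the target population for efficacy analysis".

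Section 15.3 deals with withdrawals during the study and lists last observation carried forward, observed cases and failure scoring. The third reads "Discontinuation and dropout cases will be analyzed as treatment failure cases (bacteremia cases/ Failure". The section closes by assigning failure scoring to the primary endpoint. It does not name the population to which the rule applies.

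**The concern.** The sample size and the scoring rule were set separately. The calculation treats every analysed recipient as having a 10% chance of an event. Under 15.3 the scored event is bacteremia, or discontinuation or dropout. Any dosed recipient lost before one month therefore adds a certain event, and the scored rate is above 10% even if the true bacteremia rate is exactly 10%.

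Success allows only four or five events, so each scored dropout uses a large share of the margin. The stated 80% is what a reader will rely on when judging a non-significant result. If the real figure is lower, a failed test says less about the treatment than the protocol implies.

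**Working it through.** **Inputs.** Threshold p0 = 0.30, expected rate p1 = 0.10, two-sided 5%, power 80% (Overview, 7.2); chi-square test on the FAS (15.5.1); failure scoring of dropouts (15.3).

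**1. The plan's own figure.** One-sample normal approximation with the null variance in the critical region:

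n = [(1.960·√(0.3·0.7) + 0.842·√(0.1·0.9)) / (0.3 − 0.1)]² = [(0.898 + 0.252) / 0.2]² = 33.1, rounded up to 34.

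The protocol's 34 is reproduced. Its 80% is a normal-approximation value.

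**2. Who uses the allowance.** If 37 enroll and three are never infused, 15.2.1 removes those three and 34 remain, which is the calculated number.

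**3. Success boundary.** The test rejects in favour of a lower rate when (0.3n − x)/√(0.21n) ≥ 1.960.
- n = 34: x = 4 gives (10.2 − 4)/2.672 = 2.32; x = 5 gives 1.95. At most 4 events.
- n = 37: x = 5 gives (11.1 − 5)/2.787 = 2.19; x = 6 gives 1.83. At most 5 events.

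An exact test at one-sided 0.025 has the same boundaries at both sizes.

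**4. Exact power at a true 10%.** With k dosed recipients scored as failures among n in the FAS and boundary c, at most c − k true events are allowed among the other n − k. Power is P(Bin(n − k, 0.1) ≤ c − k).

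| Scored dosed dropouts (k) | 34 in FAS, c = 4 | 37 in FAS, c = 5 |
|---|---|---|
| 0 | P(Bin(34) ≤ 4) = 75.0% | P(Bin(37) ≤ 5) = 84.0% |
| 1 | P(Bin(33) ≤ 3) = 57.7% | P(Bin(36) ≤ 4) = 71.1% |
| 2 | P(Bin(32) ≤ 2) = 36.7% | P(Bin(35) ≤ 3) = 53.1% |

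**5. Why the fall is steep.** With 34 in the FAS, one scored dropout raises the expected scored rate to (1 + 0.1·33)/34 = 12.6%, and two raise it to (2 + 0.1·32)/34 = 15.3%. The plan was sized for 10%.

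**6. Two separate causes.** The gap from 80% to 75% at 34 has nothing to do with dropout. It comes from the normal approximation against the exact binomial, with 34 lying just below a step in the boundary. With 35 or 36 in the FAS the chi-square rule allows 5 events and exact power is 86.8% or 85.5%. The falls down each column come from failure scoring alone.

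**The case against.** The best defence is that the allowance and 15.3 concern different recipients. The allowance is for losses around enrollment, the FAS requires infusion on postoperative day 3, and the missing-data rule operates inside that set. This stands.

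It also disposes of a stronger reading that a reader might infer: that the three anticipated dropouts are themselves scored as bacteremia, so that power falls to P(Bin(34, 0.1) ≤ 2) = 33%. That figure needs all 37 recipients infused and three then lost before one month. The protocol anticipates no such losses.

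A reader might also argue from section 11.1, which lists reasons for stopping that can arise before infusion, such as "In addition to 1) above, if protocol treatment is no longer possible", that 15.3 scores as failures recipients whom 15.2.1 excludes. Section 11.1 does not define an analysis population. Sections 15.2.1 and 15.5.1 do, and they imply that uninfused recipients are not scored. The silence of 15.3 on its population is a point to clarify, not a contradiction.

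Two further points have weight. Section 11.2 continues observation as far as possible after protocol treatment is completed, so stopping after infusion need not leave the one-month outcome unknown. And 34 is correct by its own method.

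None of this answers the remaining point. Withdrawal of consent, adverse events and investigator judgement are all reasons for stopping in 11.1, and all can arise after infusion. The protocol's own rule then counts a failure that the sample size never allowed for.

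**Conclusion.** The concern holds in limited form. The allowance is consistent with the FAS. What is wrong is the stated power. It is 75% by exact calculation when the allowance is fully used (34 analysed) and 84% when nobody is lost before infusion (37 analysed). Under 15.3 it falls to 58% and 37%, or to 71% and 53%, with one or two dosed dropouts.

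The figures assume a true rate of 10% in recipients who are not lost, a fixed number of scored dropouts, and rejection at two-tailed 5% without continuity correction. The boundary is the same with the correction at both 34 and 37. How many dosed recipients will be lost is not stated, so the figures for one and two are illustrations and not predictions.

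**What to change.** In the Overview and section 7.2:
- Replace the single 80% with exact power: 75% with 34 analysed and 84% with 37 analysed.
- Say that the three added cases cover only enrolled recipients who are not infused.
- Report power with one or two dosed dropouts scored as failures: 58% and 37% with 34 in the FAS, 71% and 53% with 37.

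In section 15.3, state for clarity that failure scoring applies within the FAS.

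This is wording only. The target stays at 37. The one cost is a less favourable power statement.

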## 試験デザイン

[figure not shown]

## Observation and Inspection Schedule

Recipient.

| 観察日・
評価日 | 同意取得     | スクリーニング  | 術前検査     | 登録       | 手術日 | 細胞投与日 | 細胞投与日 | 4日後  | 5日後   | 1週間後 | 2週間後 | 4週間後 | 8週間後 | 12週間後 | 6か月後 | 以後6か月毎3年まで |
|-------------|----------|----------|----------|----------|-----|-------|-------|------|-------|------|------|------|------|-------|------|------------|
| 許容範囲        | 手術前4週間以内 | 手術前4週間以内 | 手術前4週間以内 | 手術前4週間以内 |     | 投与前   | 投与後   | 投与翌日 | 投与2日後 | ±2日  | ±2日  | ±1週  | ±1週  | ±1週   | ±8週  | ±8週        |
| 同意取得        | ○        |          |          |          |     |       |       |      |       |      |      |      |      |       |      |            |
| 登録          |          |          |          | ○        |     |       |       |      |       |      |      |      |      |       |      |            |
| 被験者情報       |          | ○        |          |          | ○   |       |       |      |       |      |      |      |      |       |      |            |
| 臨床症状        |          |          | ○        |          |     | ○     | ○     | ○    | ○     | ○    | ○    | ○    | ○    | ○     | ○    | ○          |
| バイタルサイン     |          |          | ○        |          |     | ○     | ○     | ○    | ○     | ○    | ○    | ○    | ○    | ○     | ○    | ○          |
| 血液検査        |          |          | ○        |          |     | ○     | ○     | ○    | ○     | ○    | ○    | ○    | ○    | ○     | ○    | ○          |
| 尿検査         |          |          | ○        |          |     | ○     |       | ○    | ○     | ○    | ○    | ○    |      |       |      |            |
| 胸部Xp        |          |          | ○        |          |     | ○     |       | ○    | ○     | ○    | ○    | ○    |      |       |      |            |
| 培養          |          |          | ○        |          |     |       |       |      |       | ○    | ○    | ○    |      |       |      |            |
| CT          |          |          | ○        |          |     |       |       |      |       |      |      | ○    |      | ○     | ○    | ○          |
| フローサイト      |          |          | ○        |          |     | ○     |       |      |       | ○    | ○    | ○    |      |       |      |            |
| MLR         |          |          | ○        |          |     |       |       |      |       | ○    | ○    | ○    |      |       |      |            |
| 有害事象        |          |          |          |          |     |       | ○     | ○    | ○     | ○    | ○    | ○    | ○    | ○     | ○    | ○          |
| 併用治療        |          |          |          |          |     |       | ○     | ○    | ○     | ○    | ○    | ○    | ○    | ○     | ○    | ○          |

Cell donor (donor)

| Date of observation and evaluation            | Obtaining Consent         | preoperative scan | Registration | procedure |
|-----------------------------------------------|---------------------------|-------------------|--------------|-----------|
| tolerance level                               | Within 4 weeks of surgery |                   |              |           |
| Obtaining Consent                             | p-sound                   |                   |              |           |
| Subject information *                         |                           | p-sound           |              |           |
| clinical condition (of a patient's illness) * |                           | p-sound           |              |           |
| vital signs *                                 |                           | p-sound           |              |           |
| blood test *                                  |                           | p-sound           |              |           |
| Collection of donor graft liver perfusion     |                           |                   |              | p-sound   |

\*: If the patient has been observed within 3 months prior to surgery to confirm the suitability for living donor liver transplantation, the observation and examination data will be used.

## definition of a word

- Liver-derived natural killer (NK) cells

The liver is known to have a much higher content of various lymphocytes in its tissues, especially NK cells, than other organs. We have reported that liver-derived NK cells collected from normal liver have high antitumor activity against hepatocellular carcinoma cell lines.

- Vivo partial liver transplantation

Partial liver transplantation from a donor after removal of the recipient's entire liver is a fundamental treatment for non-compensated liver failure. In many other countries, brain-dead liver transplantation from brain-dead donors is common, but in Japan, partial liver transplantation from living donors is the most common procedure because of the low number of organ donations from brain-dead donors.

- Test article preparation facility

A facility with the structure, equipment, and management system for aseptic preparation of donor liver-derived lymphocytes, the test article, in accordance with the standard procedures. In this clinical study, the test material used for the protocol treatment will be prepared in the Center for Translational Medicine, Hiroshima University Hospital.

### Background (plain language).

For patients with end-stage liver failure, liver transplantation is the only treatment available. When a patient undergoes a liver transplant surgery, he or she needs to take a drug called immunosuppressant to prevent rejection. Immunosuppressive drugs lower the body's resistance to infection, making it more susceptible to infections caused by germs and viruses. Especially right after the surgery, you need a lot of immunosuppressive drugs, which increases the probability of getting a life-threatening infection.

### Content (in plain language).

The liver of a donor used in a liver transplant contains many cells (natural killer cells) that have a strong ability to attack cancer and viruses. During the liver transplant surgery, these cells are removed and cultured for three days to enhance their attacking power. On the third day after the liver transplant, the activated natural killer cells are injected into the recipient. Natural killer cells are relatively resistant to immunosuppressive drugs and are expected to be effective in preventing infections immediately after surgery.

# 1 Research Objectives

The purpose of this clinical study was to evaluate whether immunostimulatory therapy using activated natural killer (NK) cells derived from liver donor on day 3 after living donor partial liver transplantation can reduce the incidence of severe infections after liver transplantation in patients with uncompensated cirrhosis for whom no other treatment is available. This is an open-label study to compare the results. In this study, we will investigate the frequency of bloodstream infection (bacteremia) after liver transplantation and the safety of NK cell administration.

## 2 warp and woof

### 2.1 Target disease

Patients with uncompensated cirrhosis requiring liver transplantation

#### 2.1.1 Concepts, definitions, etiology, and pathogenesis

Liver transplantation is the only curative treatment for uncompensated cirrhosis, and in recent years, post-transplant outcomes have improved significantly due to standardization of the procedure, advances in immunosuppressive agents, and improved perioperative management. In recent years, however, post-transplant outcomes have improved significantly due to standardization of surgical techniques, advances in immunosuppressive agents, and improved perioperative management. Bloodstream infection is a condition in which infection spreads from local to systemic and is defined as bacteremia with clinical symptoms (CDC guidelines). The prognosis of bacterial and fungal bloodstream infections is poor, especially in the early postoperative period under strong immunosuppression, and is one of the issues that must be overcome to further improve transplantation outcomes.

#### 2.1.2 epidemiology

Sixty to eighty percent of liver transplant recipients will experience some type of infection within the first year after surgery. Most of these infections are curable, but some are fatal.(Colonna et al., Arch Surg, 123,p.360, 1988; Kawecki et al., Med Sci Monit, 15,p.CR628, 2009) The breakdown of infections is as follows About half of the infections are bacterial, 40% are viral, and 10% are fungal.(Fishman & Rubin, N Engl J Med, 338,p.1741, 1998; ) This is especially true within the first month after transplant. In particular, the frequency of infections is highest within the first

month after transplantation. Bloodstream infections have been reported to be responsible for 30% of post-transplant deaths. The most common causes of bacteremia are central venous catheter infection (30%), cholangitis (30%), and intra-abdominal infection (23%), with Gram-positive cocci and Gram-negative rods being the most commonly detected organisms.( ) The most common species detected are gram-positive cocci and gram-negative rods.

### 2.1.3 Standard treatment and prognosis

Prophylactic antibacterial and antifungal therapy for bacterial and fungal infections after liver transplantation has little evidence based on randomized clinical trials, and there is no consensus on the choice of drugs and methods. Although the drug of choice varies by institution, most institutions use a single 2-3 generation cephalosporin for 2-3 days of prophylaxis.(Soave, Clin Infect Dis, 33 Suppl 1,p.S26, 2001) The choice of drug varies by institution, but most institutions use a single 2-3 generation cephalosporin for 2-3 days of prophylaxis.

### 2.1.4 Basis for setting target diseases

Infectious diseases are the leading cause of death after liver transplantation, and the objective of this study is to reduce deaths due to infectious diseases. The aim of this study is to reduce the number of deaths due to infections. Since bacteremia is generally regarded as a serious prognostic factor among infections after liver transplantation, this clinical study will focus on bacteremia in the early postoperative period.

## 2.2 Name of the specified cell processing product and its outline

### 2.2.1 Name of specified cell processing product

Activated natural killer (NK) cells from liver transplant donor livers

### 2.2.2 Overview of the test object

For living donor partial liver transplantation, transportal hepatic perfusion of the grafted liver is mandatory for prevention of GVHD (graft-versus-host disease) and organ preservation. The liver perfusion fluid, which is usually discarded, contains a much higher concentration of liver-derived lymphocytes (T cells, B cells, NK cells, and NKT cells) compared to peripheral blood. By culturing these liver-derived lymphocytes in the presence of IL-2 (100 IU/ml) for 3 days, it is possible to induce proliferation and activation of the NK cell fraction. Activated NK cells contained in

activated intrahepatic lymphocytes have been confirmed to have high cytotoxic activity against hepatoma cell lines in vitro. In addition, 70% hepatectomy in mice induces a decrease in the expression of cytotoxic molecules of intrahepatic NK cells, and when a hepatocellular carcinoma tumor line is administered through the portal vein, cancerous tissue is observed to grow in the liver (intrahepatic metastasis model). We have confirmed that NK cells in the perfusate of the liver of normal mice can be activated and administered to the mice to inhibit cancer growth. Since NK cells are the most abundant fraction of activated liver-derived lymphocytes, but there is also a T cell fraction that can induce GVHD, anti-CD3 antibody (1 µg/ml) is added to the culture medium 1 day before administration to remove CD3-positive T cells.

The advantages of these cells are the use of donor liver perfusate, which is essential for surgical procedures and is usually discarded, and the ability to preferentially grow NK cells, which are highly cytotoxic as well as active, by simple in vitro culture. Therefore, cell collection is not invasive, and clinical application is relatively easy.

